## Abstract

**Background:**

Research published to date on the relationship between insulin resistance (IR) and fructose consumption is scarce, has used different methods, and has yielded sometimes contradictory results. This study aims to determine whether a low-fructose and/or low-sucrose diet supervised by a physician or nurse decreases IR compared to a standard diet.

**Methods/design:**

This field trial is located at primary care centers. The participants are adults aged 29 to 66 years, with a Body mass Index (BMI) between 29 and 40.99 kg/m^2^ and without diabetes. To date, 245 participants have been assigned randomly to the low-fructose diet intervention group (LFDI) at health centers in the western health service zone of Tenerife island, and 245 to the standard-diet control group (SDC) at health centers in the eastern health service zone. Recruitment is opportunistic and is carried out by physicians and nurses at participating health centers. Initially (baseline), and after 24 weeks of intervention, dietary records, physical activity, waist circumference, BMI, blood pressure, fasting blood glucose and insulin concentrations (HOMA2-IR) and lipid profile are recorded; blood glucose and insulin and lipid profile are also recorded 2 h after a 75-g glucose overload. After 48 weeks (24 weeks after the intervention), fasting blood samples are again obtained and a physical examination is performed. All tests and measures are repeated and recorded except dietary records, physical activity and oral glucose overload. Low-fructose diets are designed by calculating free and total (free + fructose associated with sucrose) fructose contents in standard diets, and removing foods with a fructose content in the highest quartile for the amounts in the standard diet.

Participants in both groups are prescribed a diet that contains 30 to 40% less than the participant’s energy requirements. The primary endpoint is change in HOMA2-IR between baseline and week 24, and other outcomes are change in HDL-cholesterol, LDL-cholesterol, triglycerides , waist circumference to height ratio and BMI. The secondary endpoint is change in HOMA2-IR between week 24 and week 48 together with the outcomes noted above. Comparisons between groups for variables used to indicate IR levels are done with a Student’s *t* test for unpaired variables or the Mann-Whitney *U* test if the distribution is not normal. Multivariate regression models will be used to control for confounding factors not accounted for in the study design, and for independent prognostic factors.

**Discussion:**

If the dietary intervention being tested, i.e., a diet low in fructose/sucrose, is able to reduce IR, the results – if translated into regular clinical practice – could provide a hitherto unavailable tool to prevent type-2 diabetes mellitus.

**Trial registration:**

ISRCTN, ID: ISRCTN41579277. Registered retrospectively on 15 November 2016.

**Electronic supplementary material:**

The online version of this article (doi:10.1186/s13063-017-2043-z) contains supplementary material, which is available to authorized users.

## Background

The worldwide obesity epidemic currently affecting industrialized countries is causing high rates of morbidity and mortality from related diseases and disorders such as diabetes and cardiovascular disease. The influence of suboptimal dietary habits in the appearance of obesity has led many researchers to study the hypothetical role of fructose. One systematic review failed to find support for an effect of fructose on increases in body weight [1]. However, the short follow-up period for most participants, for a mean of 4 weeks in trials with an isocaloric diet and 1.5 weeks in those with a hypercaloric diet, was a major source of uncertainty according to the authors of this review. Other sources of uncertainty noted were heterogeneity among groups of participants (13 trials involved patients with diabetes, 7 involved patients with overweight or obesity, and 21 involved patients with normal body weight), the low number of participants in many trials (13 included 10 participants or fewer, 12 included 11 to 25, and only 5 included more than 25 participants), and the sensitivity to imputations in crossover trials. Nevertheless, the association between excess lipid storage as manifested by obesity and insulin resistance (IR) has long been recognized [2]. Insulin resistance is a metabolic situation characterized by a decrease in the physiological response of peripheral tissues to the action of insulin for cell nutrition and the maintenance of glucose homeostasis. This indicator is strongly predictive of type-2 diabetes mellitus (DM) and cardiovascular disease [3].

The role of fructose in the development of IR in the liver is controversial. This monosaccharide is present especially in fruit, and has become a widely used additive in many food industry products such as soft drinks and nonalcoholic beverages, generally in the form of fructose-enriched corn syrup [4]. Moreover, most frequently consumed manufactured food products contain sucrose as an additive; this disaccharide consists of equal proportions of fructose and glucose.

Different mechanisms have been proposed to explain the effect of fructose versus glucose consumption on the appearance of IR. One mechanism is related to the liver metabolism of each monosaccharide. Excessive fructose consumption increases de-novo lipogenesis and can lead to dyslipidemia, increased visceral fat, overweight and obesity. Glucose metabolism in the liver may limit the production of substrates characteristic of de-novo lipogenesis since this is regulated by phosphofructokinase which is inhibited by ATP and citrate under conditions of energy intake above the individual’s requirements. However, fructose is metabolized in the liver via fructokinase in a manner independent of energy status, and so lacks the limiting control mechanism that operates for glucose. A consequence is that the consumption of large amounts of fructose does not halt de-novo lipogenesis; this, in turn, can increase the amount of hepatic fat and thus induce IR in the liver [5]. Another proposed mechanism is related to the possible satiating effect of fructose. Consumption of this sugar stimulates insulin secretion which, in turn, leads to leptin release from adipocytes and the inhibition of ghrelin secretion in the gastrointestinal tract. These changes stimulate brain centers that regulate satiety and energy homeostasis. However, fructose consumption does not lead to acute stimulation of insulin secretion which would attenuate the stimulation of leptin secretion and ghrelin inhibition. These effects, in turn, influence the regulatory action of these hormones on energy balance in the central nervous system. In people who consume large amounts of fructose, the lower circulating levels of insulin and leptin together with increased ghrelin concentration may lead to increased calorie intake, thereby contributing to weight gain and obesity when high-fructose diets are consumed chronically [6]. Page and colleagues showed that glucose but not fructose consumption reduced activation of the hypothalamus, insula and striatum – brain regions that regulate appetite, motivation and reward processing [7].

Several recent epidemiological studies have suggested a plausible relationship between fructose consumption and IR. Thus far, interventions have been tested to increase and decrease fructose consumption. In two separate studies Aeberli and colleagues. found that even with moderate levels of fructose or sucrose consumption (40 and 80 g, respectively) compared to moderate glucose consumption (40 g), atherogenic low-density lipoprotein (LDL) particles were increased along with total and LDL-cholesterol, and IR in the liver. However, they found no differences in IR (HOMA2-IR), possibly because of the short duration of the study (3 weeks) [8, 9]. Stanhope and colleagues also found increases in LDL-cholesterol, non-high-density lipoprotein (HDL)-cholesterol, apolipoprotein B, postprandial triglycerides, cholesterol and remnant triglycerides, as well as small dense LDL-cholesterol, in persons who obtained 25% of their energy requirements from beverages sweetened with fructose-enriched corn syrup compared to persons who consumed a glucose-rich diet [10]. Maersk and colleagues studied 17 men and 30 women with overweight for a 6-month period to compare the influence of a sucrose-rich beverage (20% of total energy requirements) with three isocaloric diets (one with low-fat milk, one with aspartate as a beverage sweetener, and one with water). They found increases in visceral fat, liver and muscle triglycerides and elevated fasting plasma triglyceride levels. Interestingly, these effects were not accompanied by changes in body weight [11].

Most trials designed to reduce fructose consumption have involved children and adolescents as frequent consumers of sugar-rich beverages. A controlled double-blind trial that enrolled children showed that a dietary education programs designed to reduce sugar and fructose consumption by substituting low-calorie sweetened beverages for sugar-containing beverages had beneficial effects on Body Mass Index (BMI) [12]. A randomized trial that followed with overweight and obesity for 2 years found that the increase in BMI was smaller in participants who consumed fewer sugar-sweetened beverages [13]. Neither of these trials investigated IR, and calorie intakes in the intervention group were lower than in the control group. Another trial with African-American and Latino adolescents found that reducing the consumption of added sugar improved insulin sensitivity even when body weight or body fat was not reduced [14]. In that study, calorie intake in terms of kcal/day was again higher in the control group than in the two intervention groups (nutrition education, and nutrition education plus strength training). The only study in adults that we are aware of was designed to analyze the effect of decreased fructose consumption on body weight and IR [15]. This study compared two isocaloric diets with no added sugars but containing different amounts of fructose (≤20 g versus 50–70 g). The decrease in BMI was greater in the latter group, and IR (HOMA) was also lower although the difference between groups was not statistically significant (*p* = 0.12).

In light of the gaps in our current knowledge, we designed a field trial to test the effects of decreased fructose consumption on IR under real-life conditions in participants who consume an isocaloric diet.

We describe here a single-blind, multicentre, randomized controlled field trial lasting 24 weeks that is being carried out at primary health care centers, designated the DISFRUTE (DISminución de la FRUctosa en TEnerife, i.e., Decrease in fructose in Tenerife) study. The aim of the trial is to determine whether a decrease in dietary free or sucrose-associated fructose is effective in decreasing IR.

## Methods/design

The *primary objective* of this study is to determine whether decreasing the consumption of foods rich in fructose or sucrose leads to a decrease in IR after 24 weeks in a population with obesity, independent of a reduction in calorie intake.

The *secondary objective* is to determine whether after 48 weeks (24 weeks after the end of the intervention according to protocol), IR levels remain unchanged compared to the end of the 24-week intervention period.

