### Statistical analysis

Before-after changes in IR, laboratory indicators and anthropometric values are determined with Student’s *t* test for paired samples. Comparisons between the intervention and control groups for variables indicative of IR are done with Student’s *t* test for independent samples when the frequency distribution is normal, or with the Mann-Whitney *U* test when the distribution is not normal. For these comparisons multiple linear or regression models are used as appropriate to detect possible confounders or independent prognostic factors for IR that are not controlled for in the trial design. Student’s *t* test for paired samples will be used to analyze changes between week 0 and week 24 in the main outcome variables in each group (HOMA2-IR, fasting blood glucose and insulin, and these same measures after an oral glucose overload) and the secondary outcomes (fasting LDL-cholesterol, HDL-cholesterol and triglycerides, and these same measures after a glucose overload; waist circumference, waist to height ratio, BMI and blood pressure). To verify compliance with the recommended diets the same analysis will be done for total calorie intake and individual nutrient intakes. These analyses will record results for the variables noted above between week 24 and week 48, and between week 0 and week 48. Student’s *t* test for independent samples will be used to analyze the differences between groups observed from week 0 to week 24 for the variables noted above. As potential confounders we will consider calorie intake, variations in nutrient intakes other than fructose, and physical activity. If differences are detected between groups at the start of the study in HOMA2-IR, any nutrient intake or physical activity, appropriate adjustment will be used in the outcomes analysis. An intention-to-treat analysis will be done taking into account losses to follow-up, and using the most recent changes and measurements available for participants who did not complete the study. All hypothesis tests will be two-sided with a significance level of *p* < 0.05, and all statistical analyses will be done with the NT Professional v. 21.0 (IBM) statistical package (SPSS) for PCs in a Windows environment. More specific information about the trial and protocol is summarized in the Standard Protocol Items: Recommendations for Interventional Trials (SPIRIT) Checklist (Additional file 5).

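### The secondary objective is a no-change claim to week 48, but the plan gives only tests for a difference, and carrying last values forward would pull the estimate towards no change

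*Protocol article*

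**What the plan says.** The objectives, at the start of Methods/design, ask whether after 48 weeks "IR levels remain unchanged compared to the end of the 24-week intervention period". The Abstract gives the matching endpoint: "The secondary endpoint is change in HOMA2-IR between week 24 and week 48".

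The Statistical analysis section plans a within-group analysis: "test for paired samples will be used to analyze changes between week 0 and week 24 in the main outcome variables in each group". It extends the post-load measures, lipids, anthropometry and dietary intakes to the same treatment, and then adds: "These analyses will record results for the variables noted above between week 24 and week 48, and between week 0 and week 48". For the comparison of arms, the detailed text names one period: "test for independent samples will be used to analyze the differences between groups observed from week 0 to week 24". On level and sidedness: "All hypothesis tests will be two-sided with a significance level of" p < 0.05. For participants who do not finish, the intention-to-treat analysis takes the latest changes and measurements on file.

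The Design section places HOMA2-IR at baseline and at weeks 24 and 48 only. On week 48 the Abstract says: "All tests and measures are repeated and recorded except dietary records, physical activity and oral glucose overload".

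**The concern.** A difference test can show that insulin resistance (IR) moved after week 24. It cannot show that it stayed put, because a non-significant result is what one gets both from stability and from too little information. The plan pairs a no-change question with that kind of test alone and gives no margin or confidence-interval criterion.

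Three further features bear on the same analysis:
- The missing-data rule can insert changes of exactly zero into the week 24-48 analysis.
- A within-group result does not say whether any advantage of the low-fructose diet over control lasts, and the between-group test at week 48 is not clearly assigned.
- Part of the listed week-48 analysis uses data that are not collected at that visit.

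At stake is a statement that the effect is durable, made on evidence that cannot carry it.

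**Working it through.** **Inputs.** From Design: 245 per group, 20% loss, HOMA2-IR at weeks 0, 24 and 48. From Statistical analysis: paired t test, two-sided 0.05. No SD of HOMA2-IR change is given, so a true change d is expressed in SDs of the individual week 24-48 changes (assumption).

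**The plan's own figure.** There is none for this objective. The stated size rests on 4 kg of body weight without an SD, so it cannot be rebuilt directly. It matches 196 / (1 - 0.20) = 245 only if an SD of about 14.1 kg is assumed. What carries over is 245 x 0.80 = 196 pairs, taking the 20% to apply at week 48.

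**Chance of a non-significant paired test.** P = 1 - P(|Z + d√n| > 1.96). With n = 196, √n = 14:
- d = 0.10: d√n = 1.4, P = Φ(0.56) - Φ(-3.36) = 0.71
- d = 0.15: d√n = 2.1, P = Φ(-0.14) = 0.44
- d = 0.20: d√n = 2.8, P = Φ(-0.84) = 0.20

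The noncentral t distribution agrees to within about one percentage point:

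| Pairs | 0.10 SD | 0.15 SD | 0.20 SD | 0.30 SD |
|---|---|---|---|---|
| 245 | 66% | 35% | 12% | 0.3% |
| 196 | 71% | 45% | 20% | 1.3% |
| 100 | 83% | 68% | 49% | 16% |

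The row for 100 pairs illustrates poor week-48 attendance. It means a loss of 1 - 100/245 = 59%, well above the planned 20%.

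**Carry-forward.** With no HOMA2-IR between weeks 24 and 48, anyone without a week-48 sample has a carried-forward change of zero. The same holds for someone with baseline only. For a share f of zeros, the mean is (1 - f)d and the variance is (1 - f)(1 + d²) - [(1 - f)d]². With f = 0.20, d = 0.20 and 245 analysed, and loss unrelated to the change:
- mean = 0.80 x 0.20 = 0.16
- variance = 0.80 x 1.04 - 0.0256 = 0.806, SD = 0.898
- 95% CI half-width = 1.96 x 0.898 / √245 = 0.11
- 196 completers alone: mean 0.20, half-width 1.96 / 14 = 0.14
- miss rate with zeros: 0.16 / (0.898 / √245) = 2.79, Φ(1.96 - 2.79) = 0.20, the same as for completers alone

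Simulation gives the same picture. With 40% zeros the estimate is 0.12 SD with half-width 0.10, against 0.20 SD and 0.16 for completers. Both analyses miss the change 33% of the time.

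**What margin the planned size supports.** For two one-sided tests (90% CI inside the margin), 80% power and true change zero, margin = (1.645 + 1.282) / √196 = 0.21 SD. For a 95% CI rule, (1.960 + 1.282) / 14 = 0.23 SD. If carried-forward zeros stayed in and the true change equalled a margin of 0.20 to 0.30 SD, the 90% CI rule would falsely declare no change in 18-27% of trials with 20% zeros and 49-77% with 40% zeros. For completers the figure is about 5%.

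**Variables at week 48.** The sentence on weeks 24-48 and 0-48 refers back to a list that includes post-load glucose, insulin and lipids, and calorie and nutrient intakes. The Abstract excludes the glucose load and dietary records at week 48, and Data recording and analysis places food diaries at weeks 0 and 24 only. The two cannot both hold.

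**The case against.** The strongest reply is that no decision rule is stated. The objective asks neutrally whether IR stays the same, the endpoint is a change that can be reported as an estimate, and a margin could sit in an analysis plan that is not shown. This is right as far as it goes: a reader might infer that p ≥ 0.05 will be read as no change, but the protocol never says so. What stands is that the protocol itself fixes the objective, the test and the missing-data rule, and these do not fit together.

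A reader might also infer that durability against control is not tested at all. The documents do not support that. The Abstract and the opening of Statistical analysis both describe between-group comparisons of IR variables without a time limit. Only the detailed text ties the independent-samples test to weeks 0 to 24, so the week-48 comparison is unclear rather than absent. Any such test would still be one for a difference.

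It is fair, too, that the planned size is not small for this purpose: 196 pairs detect 0.20 SD with about 80% power, and nothing in the document shows that 0.10 SD matters clinically. Nor do carried-forward zeros make a non-significant result more likely than losing those patients would. Their separate harm is the shrunken estimate and the narrow interval. Finally, the missing-data wording is ambiguous: carrying a measurement forward gives zero, carrying a change forward need not.

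The variable list is a drafting slip that leaves HOMA2-IR untouched, but it remains a contradiction in the text.

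**Conclusion.** The point holds in this form: a no-change objective is served only by tests for a difference, with no other criterion, so a non-significant result could not support it. For modest changes the gap is material. At 196 pairs, 0.10 SD is missed about 71% of the time and 0.15 SD about 44%, but 0.20 SD only about 20%. If measurements are carried forward, the estimated change shrinks by the missing share (0.20 to 0.16 SD with 20% missing) and its interval narrows towards no change. The week-48 between-group comparison needs to be stated, and part of the listed week-48 analysis cannot be done.

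These figures assume SD units for the change, 20% loss by week 48, and loss unrelated to the change. They do not support a claim that the plan will declare stability from p ≥ 0.05, or that its planned numbers are too few to find a change of 0.20 SD or more. The objective is secondary, so the change should be made, but the week-24 primary comparison does not depend on it.

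**What to change.** 1. Report the between-group difference in HOMA2-IR at week 48, adjusted for baseline HOMA2-IR, with a 95% CI.
2. Report the within-group week 24-48 change with its CI. Describe IR as unchanged only if that CI lies wholly inside a margin fixed before week-48 data are examined. State whether the 90% or the 95% CI is used. Otherwise give the estimate and call the question inconclusive.
3. Use no carried-forward values in either analysis. Use observed data in a mixed model for repeated measures, or multiple imputation. The protocol contains neither, so one has to be adopted. Adding a margin while keeping the zeros would make false claims of no change more likely.
4. Limit the week 24-48 and week 0-48 analyses to variables measured at week 48, and reconcile the Statistical analysis text with the Abstract.

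The cost is analysis wording, one margin and a change of missing-data method, with no new data. The drawback is that durability may have to be reported as inconclusive: 196 completers support a margin of about 0.21 SD at 80% power with the 90% CI, and a 95% CI rule needs a wider one, about 0.23 SD.

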### Design

A single-blind, multicenter, randomized controlled **f**ield trial with two groups of participants (low fructose/sucrose diet versus standard diet) recruited at primary care health centers in Tenerife island (Canary Islands, Spain). Sample size: because of the lack of consensus in the academic literature regarding the cutoff value of HOMA2-IR that defines the presence of IR, we opted to use body weight change. We estimated a mean weight loss of 4 kg (1.43 kg/m^2^ BMI assuming a mean height of 1.67 m for the Canary Islands’ population [16]), a significance level of *p* ≤ 0.05, 80% power and a 20% dropout/loss to follow-up rate. A weight loss of 4 kg was estimated based on maximum weight loss in the only interventional trial reported to date of the effect of lower fructose consumption on body weight and IR [15]. Dietary intervention trials aimed at studying weight loss have reported similar amounts of weight loss after 6 months [17]. In the trial reported here, in which both groups consume an isocaloric diet, we do not anticipate differences between the groups in the amount of weight lost. Based on these calculations our estimated sample size for each of the two groups is 245 participants.

The primary outcome measure is insulin resistance (IR) which is estimated from fasting serum glucose and insulin concentrations with the computer-based Homeostasis Model Assessment system (HOMA2-IR) at baseline, 24 and 48 weeks. The secondary outcomes are BMI, waist circumference (waist to height ratio) and blood pressure which are measured at baseline, 4, 8, 12, 16, 20, 24 and 48 weeks, and total cholesterol, HDL-cholesterol, LDL-cholesterol and triglycerides which are measured at baseline, 24 and 48 weeks.

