### Randomization

Participants are randomized by health care zone. Patients in the low-fructose diet intervention group (LFDI) are assigned to health centers in the western zone of Tenerife island, and patients in the Canary Islands Health Service standard-diet control (SDC) group are assigned to the eastern zone of the island. This randomization system is used to prevent contamination bias. If patients randomized to both groups attended the same health center this source of bias would be difficult to avoid because many patients in the LFDI group are likely to have relatives or friends in the SDC group, and vice versa. Contamination could also occur between staff members at a given health center. Sixteen primary health centers are participating in this study; all of them belong to the same health care administration district (Gerencia de Atención Primaria de Tenerife). Given that the total area of the island of Tenerife is relatively small, the characteristics of the population served by all health centers are assumed to be similar. The longest distance between participating health centers is 64 km. All centers and staff provide the same suite of services. The variations between centers in the catchment population assigned and the numbers of patients under each staff physician’s and nurse’s care are similar. We therefore do not anticipate between-group differences in the baseline data or systematic biases in the results of the care provided at different centers.

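### The stated 80% power with 245 per arm lists dropout as its only allowance, so it is not supported under allocation by zone through 16 health centers

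*Protocol article*

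**What the plan says.** **Sample size (protocol article, Design).** The inputs are a weight loss ("We estimated a mean weight loss of 4 kg"), a significance level of 0.05, and "80% power and a 20% dropout/loss to follow-up rate". The result is given directly: "Based on these calculations our estimated sample size for each of the two groups is 245 participants". No SD, ICC, cluster size or design effect appears among the inputs. The same paragraph says of weight that "we do not anticipate differences between the groups in the amount of weight lost".

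**Allocation (Randomization).** "Participants are randomized by health care zone". The west receives the low-fructose diet: "Patients in the low-fructose diet intervention group (LFDI) are assigned to health centers in the western zone of Tenerife island". The east receives the standard diet. The number of clusters is given ("Sixteen primary health centers are participating in this study"), but not how many lie in each zone. The section argues that the centers serve similar populations with similar services. It separates the diets by zone because relatives, friends and staff at one center could influence each other.

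**Analysis (Statistical analysis).** The between-group comparison is an independent-samples t test, or Mann-Whitney if the data are not normal, with regression for confounders. The confounders named do not include center or zone. "All hypothesis tests will be two-sided with a significance level of *p* < 0.05".

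**The concern.** When every patient at a center receives the same diet, outcomes within a center tend to be correlated, because patients share staff, counseling style and local habits. The variance of the difference between arms is then multiplied by 1 + (m - 1) x ICC, where m is the number of analyzed patients per center. A size obtained from effect, significance level, power and dropout alone carries no such factor. If 245 per arm was set to reach 80% on those inputs, any positive ICC brings the power of a valid test below 80%.

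This concerns the allocation and not the choice of sizing variable. Repeating the calculation for HOMA2-IR with an individual-level formula would leave the gap in place.

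Two misreadings are at stake. If clustering is respected in the analysis, a null result could be taken as coming from a trial with 80% power when it had less. If clustering is ignored, a significant result could be taken at the 5% level when the true error rate is higher.

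**Working it through.** **Inputs from the article:** 245 per arm, 20% dropout, 80% power, two-sided 0.05, 4 kg (1.43 kg/m² BMI), 16 centers.

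**Assumptions, not in the article:** 8 centers per arm; ICC 0.01 to 0.05; the 4 kg treated as a between-arm difference; 245 calibrated to exactly 80% under individual allocation.

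**1. The plan's own figure.** Completers: 245 x 0.80 = 196 per arm. The BMI conversion is right: 4/1.67² = 1.43. Without an SD, 245 cannot be reproduced forwards. Solving backwards with the two-mean formula:
- detectable standardized difference d = (1.960 + 0.842) x sqrt(2/196) = 2.8016 x 0.1010 = 0.283
- implied SD = 4/0.283 = 14.1 kg, or 1.43/0.283 = 5.05 kg/m²

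Neither SD is stated.

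**2. Design effect.** m = 196/8 = 24.5, so DE = 1 + 23.5 x ICC, and effective n = 196/DE.

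**3. Power of a test that allows for center.** Normal reference: Phi(2.8016/sqrt(DE) - 1.96). Center-level reference: noncentral t with 16 - 2 = 14 degrees of freedom and noncentrality 2.8016/sqrt(DE).

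**4. The unclustered test.** Its standard error is too small by sqrt(DE). Type I error = 2 x [1 - Phi(1.96/sqrt(DE))]. Rejection probability at d = 0.283 is about Phi(0.8416/sqrt(DE)).

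| ICC | DE | Effective n per arm | Power, normal | Power, 14 df | Type I error, unclustered | Rejection at d = 0.283, unclustered |
|---|---|---|---|---|---|---|
| 0 | 1.000 | 196 | 80% | 74% | 5.0% | 80% |
| 0.01 | 1.235 | 159 | 71% | 65% | 7.8% | 78% |
| 0.02 | 1.470 | 133 | 64% | 58% | 10.6% | 76% |
| 0.05 | 2.175 | 90 | 48% | 42% | 18.4% | 72% |

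**5. Detectable standardized difference at 80% power.** Normal reference: 0.283 x sqrt(DE) = 0.315, 0.343 and 0.417 at ICC 0.01, 0.02 and 0.05. On 14 df the multiplier 2.8016 becomes 3.013, the noncentrality that gives 80% power. The values are then 0.338, 0.369 and 0.449, against 0.304 at ICC 0.

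**6. Sensitivity to the calibration.** If the SD for the 4 kg difference were 10 kg, the individual formula needs 2 x (2.8016 x 10/4)² = 98 completers per arm. Then 196/98 is about 2.0, and 80% (normal reference) holds up to an ICC of about (2.0 - 1)/23.5 = 0.042. At ICC 0.01 the power would be about 95%. With SD 12 kg, 141 completers are needed and 80% holds up to an ICC of about 0.016.

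**7. Zone level.** With one zone per arm, the difference between zones cannot be separated from the difference between diets. The center calculation does not include it.

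**The case against.** The strongest reply is that the loss is not established. With no SD stated, nobody can show that 245 was the bare minimum for individual allocation. At an SD of 10 or 12 kg it would hold a margin that absorbs some clustering. This stands. A reader might infer that power falls below 80% for every endpoint, or that the true power is 48% to 71%. The article supports neither, because those figures rest on the calibration and on assumed ICCs. What remains is that a margin, if there is one, is neither stated nor derived.

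Second, the 80% is attached to weight, not to HOMA2-IR, and the 4 kg is described as a mean loss rather than a difference between arms. This also stands. A reader might infer that the trial claims 80% power for HOMA2-IR and misses it, but no power for HOMA2-IR is claimed anywhere. Sizing on a variable on which the arms are not expected to differ is a separate fault.

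Third, the clustered power figures describe a test that the article does not specify. True: for the t test as described, the rejection probability falls only to 78%, 76% and 72%, and the larger effect is on the type I error. That changes which error dominates, but it does not rescue the 80%, because a test run at an 8% to 18% error rate does not have 80% power at the 5% level. A fuller analysis plan may add a center term, so its absence from the article is not counted here as a fault.

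Last, the article argues that the centers are similar. Similar populations and services on average do not imply zero correlation within centers, and the article's own contamination argument expects people at one center to influence each other.

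**Conclusion.** The point holds in a limited form. The article states a power, the inputs and the resulting size; dropout is the only allowance; and the allocation is by zone through 16 centers. On those inputs 80% is not supported under that allocation, whichever outcome the calculation uses.

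The size of the loss is illustrative. It requires 196 completers per arm to give exactly 80% under individual allocation (d = 0.283, SD about 14.1 kg for 4 kg), 8 centers per arm, and an ICC between 0.01 and 0.05. Under those assumptions a cluster-valid test has 71% to 48% power, or 65% to 42% on 14 degrees of freedom. The unclustered test has a type I error of about 8% to 18%. A smaller SD would soften the loss. Variation between the two zones comes on top and cannot be quantified from this design.

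**What to change.** Add no patients and change nothing in conduct. Rewrite the power statement as follows:

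- Replace the 80% figure by the detectable between-arm difference in HOMA2-IR change from week 0 to week 24 at 196 completers per arm. Multiply the variance by 1 + (m - 1) x ICC with m about 24.5, or the actual center sizes, and use a center-level degrees-of-freedom reference (14 if all 16 centers contribute).
- State the SD of HOMA2-IR change used, and its source.
- Use the ICC of the week 0 to week 24 change, estimated from variation between centers within each arm and pooled over arms, so that no treatment comparison is shown. Otherwise show the range 0.01 to 0.05. The ICC of baseline HOMA2-IR is only a rough guide, since a change can have a different ICC from a level.
- Say that the figure holds only for an analysis that accounts for center.
- Say that with one zone per arm the zone difference is neither covered by the figure nor estimable.

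The cost is one recalculation and a rewritten paragraph. The downside is that the stated power becomes less favourable.
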